## Abstract

**Introduction:**

Dyspnoea affects 10% of the general population, and 12% of hospitalised patients report experiencing dyspnoea at rest. It is a common and distressing symptom experienced by people living with chronic obstructive pulmonary disease (COPD). Neuromodulation, which uses electrical stimulation to modulate neural pathways, is a validated clinical procedure offering a potential therapeutic approach. We speculate that non-invasive transcutaneous vagus nerve stimulation (tVNS) and trigeminal transcutaneous electric nerve stimulation (TENS) could improve dyspnoea management by targeting relevant neural circuits.

**Methods and analysis:**

We will conduct a feasibility cross-over trial in people with severe COPD and significant exertional dyspnoea referred for pulmonary rehabilitation. Patients will be recruited following the prerehabilitation assessment visit comprising a clinical evaluation and a maximal cardiopulmonary exercise testing on ergocycle. Subsequently, two study visits will be conducted within 2 weeks apart from each other. Eight participants will perform a submaximal constant work rate at 80% workload of the VO_2_ max, either with cervical tVNS (n=4) or trigeminal TENS (n=4). In a cross-over design, both patient groups will undergo sham and active treatment of the neuromodulation technique in a randomly assigned order. The main outcome will be feasibility, assessed by the percentage of patients who attend all visits and complete all tests. Secondary outcomes include other feasibility endpoints, the acceptability and suitability of the interventions (including an evaluation of sham as an exploratory outcome), and the incidence of adverse or undesirable events related to the procedures. Exploratory outcomes include changes in dyspnoea symptoms, measured using standardised questionnaires, such as Borg scale and the Visual Analogue Scale.

**Ethics and dissemination:**

The protocol is approved by the institutional research ethics committee of the *Centre intégré universitaire de santé et de services sociaux (CIUSSS) de l’Estrie*—CHUS, Sherbrooke, Quebec, Canada (#2025-5604) and follows *2013 Standard Protocol Items: Recommendations for Interventional Trials (SPIRIT)* guidelines. Results will be communicated in international meetings and submitted to peer-reviewed journals with respect to the *2010 CONsolidated Standards Of Reporting Trials (CONSORT)* statement for feasibility studies.

**Trial registration number:**

NCT06985628.

STRENGTHS AND LIMITATIONS OF THIS STUDYThis is the first study to investigate neuromodulation for alleviating dyspnoea perception in patients with chronic respiratory disease.The small sample size and cross-over design are appropriate for a feasibility trial but introduce potential learning bias and limit the interpretation of the efficacy of the interventions.Dyspnoea perception is assessed only in severe chronic obstructive pulmonary disease patients, limiting generalisability and scales used, such as Borg and Visual Analogue Scale, may not fully reflect its complex neurological dimensions.The proposed sham procedure and sham-related questionnaire are not validated but were adapted from pain studies to assess the feasibility and blinding quality in this novel context.Although the non-invasive nature of the interventions limits the specificity of neural targeting, it offers a safe and practical foundation for testing this novel approach in standardised exercise conditions.

## Introduction

 Dyspnoea is typically described as the feeling of being unable to get enough air, defined as ‘shortness of breath’, and as the distressing experience of ‘air hunger’.^1^,^3^ This symptom is highly prevalent, affecting approximately 10% of the general population, and 12% of hospitalised patients report experiencing dyspnoea at rest.^4^,^6^ Dyspnoea is associated with various serious conditions, including pulmonary fibrosis, chronic obstructive pulmonary disease (COPD), anaemia and heart failure, where it is often the major source of patient suffering.^7^,^13^ The multifaceted nature of dyspnoea makes treating its underlying cause challenging, and current therapies, such as opioids, ventilatory support and pulmonary rehabilitation, often provide insufficient relief.^14 15^ Severe dyspnoea affects 90% of individuals with COPD in their final year of life, and nearly half do not find relief with current treatments.^16 17^ This leads to persistent, debilitating breathlessness and reduced quality of life. In Quebec, 7% of medical aid in dying requests are due to lung disease.^18^ It highlights the unmet need for innovative alternatives to better address this concerning symptom.^17^

Dyspnoea, in a complex and still not entirely well-understood manner, arises from the integration of biochemical, mechanical and neurological signals, creating a mismatch between afferent inputs and efferent pulmonary responses.^17^ This highlights that, as a sensation, dyspnoea originates from neurological pathways, presenting a potential avenue for neuromodulation.^8 9 17^ The field of neuromodulation applies precisely targeted electrical inputs to interact with the nervous system, aiming to modulate pathological signal transmission, perception and integration. Neuromodulation has gained increasing interest, given its applications in various disorders, including epilepsy (via vagus nerve stimulation), pain or angina (via spinal cord stimulation) and movement disorders (via deep brain stimulation).^17^ The similarities between dyspnoea and other sensations treated with neuromodulation, such as pain, make several neuromodulation approaches compelling options to explore dyspnoea relief.^17^ Since dyspnoea serves as an alarm signal of mismatched ventilatory demands, the goal is not to suppress this signal entirely, but rather to alleviate its excessive perception, particularly in severe cases where symptom management becomes palliative.^17^ However, understanding its feasibility and relevance requires further investigation and comprehension.

Invasive vagus nerve stimulation (VNS) is approved for treating epilepsy and depression.^19^ While transcutaneous VNS (tVNS) offers a more convenient non-invasive alternative, with growing interest for its role in respiratory pathways, it remains experimental for some uses.^20^,^24^ In theory, VNS could interfere with pulmonary sensory afferents related to dyspnoea and modulate parasympathetic signals, whose hyperactivation may worsen pulmonary symptoms.^25^,^27^

Transcutaneous electric nerve stimulation (TENS) is used in physiotherapy to treat various types of pain, such as trigeminal neuralgia, among its other uses.^28^,^31^ These treatments might be linked to the gate control theory studied in chronic pain, explaining that stimulation of particular neurologic structures may inhibit the intensity of other unpleasant afferences.^17 32 33^ Stimulation of the trigeminal nerve is supported by clinical practices such as the use of fans blowing cool air on patients’ faces, hypothesising that it activates nasal cold receptors in the V2 and V3 branches of the trigeminal nerve (cranial nerve V).^1733^,^35^ This suggests it could also be applied for other purposes, such as neuromodulation of dyspnoea.^36^

There is a recognised lack of alternative treatments for severe dyspnoea, and while opioids and other dyspnoea-directed therapies are often insufficient for alleviating this sensation, as they can be for pain management, neuromodulation may present a promising alternative.^37 38^ We hypothesise that neuromodulation techniques for relieving dyspnoea will be practical and well received by participants, and we aim to detect promising hints indicating that these methods can effectively reduce the sensation of dyspnoea. The main objective of this sham-controlled randomised trial is to evaluate the feasibility of this protocol, setting the stage for larger-scale research on the effectiveness of neuromodulation techniques for dyspnoea. The comparator in this randomised trial is a sham intervention using TENS and tVNS devices set to ineffective parameters, keeping participants blinded for a plausible study design.^39^

## Methods and analysis

The project is currently recruiting and collecting data, with expected recruitment ending by 1 December 2025, data collection by 1 February 2026 and analysis by 1 May 2026.

### Trial design and study setting

We propose an observational, prospective, feasibility, cross-over trial to explore the potential of two non-invasive neuromodulation methods, tVNS and trigeminal TENS, to alleviate dyspnoea (figure 1*).* The study protocol follows the *2013 Standard Protocol Items: Recommendations for Interventional Trials (SPIRIT)* guidelines.^40^ This study employs a single-blinded format, where participants are unaware if they are receiving the sham or the real interventions, but the researchers in charge of data collection or of the analysis are not blinded. The study will be conducted at the *Centre Hospitalier Universitaire de Sherbrooke* (CHUS)’s research centre, and participants will be selected from the COPD pulmonary rehabilitation clinic at CHUS, in Quebec, Canada.

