### Study interventions

In the first arm (TENS), participants undergo submaximal CWR with the addition of a non-invasive trigeminal TENS, administered or expertly guided by a physiotherapy expert using the methods of this device. The TENS technique uses electromagnetic waves to modulate nerve transmission transcutaneously. When electrodes are placed on the skin, approximately over the temporomandibular joint, it is well established that they can modulate trigeminal nerve activity with the appropriate settings. We propose an initial configuration with a pulse duration of 60 µs at a frequency of 100 Hz, but the parameters may be adjusted during preliminary tests of the devices and for each patient as needed. For the sham trigeminal TENS, we suggest informing patients that two different modes of stimulation will be used, one of which will feel stronger than the other. This allows us to activate the device during the intervention and adjust it to a level where the skin experiences a mild tingling sensation. This stimulation will remain below the threshold of the gate control theory, being clinically ineffective, without explicitly informing the patients of this detail, in accordance with the attested consent form.^44^,^47^

In the second arm (tVNS), participants undergo submaximal CWR with the addition of cervical tVNS (*gammaCore Sapphire D Device, electroCORE*: Food and Drug Administration cleared^48 49^ and approved by *Health Canada*^50^). This technique will be applied or expertly guided by a neurosurgeon specialised in functional neurosurgery. The cervical tVNS device is applied manually to the front of the neck, near the trachea, to modulate afferent and efferent vagal nerve activity. As the *gammaCore* device is indicated and configured for the treatment of migraines, some parameters, such as a 5000 Hz pulse at 25 Hz, are fixed, while the stimulation voltage (limited to a peak of 24 V), and current (mA) remain adjustable and variable. This low-voltage VNS may be more advantageous for respiratory modulation.^51^

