Throughout the entire duration of the study, participants’ complete medication regimen will be assessed, and their medication must remain stable during the trial. As part of the pulmonary rehabilitation programme, the eight participants will undergo a medically advised first CPET at VO_2_ max following the data measurement procedures of the study. The Borg scale will be evaluated before the test, every 3 min during the test and at the end of the test. For the baseline visit, only SpO_2_ will be measured before and after CPET. Additionally, spirometry parameters, including FEV1, FVC and FEV1/FVC, will be measured before the test. Data on rehabilitation performance, such as VO_2_ max, breathing and cardiac reserve and the assessment of maximal effort testing, will be useful for the setting of the next two visits. This baseline CWR is crucial as it sets the parameters for the next two experimental visits and as it accounts for the effects of adaptation to the physical test (learning effect), ensuring that any observed changes in subsequent tests are not merely due to physiological adaptations or normal variations that occur in every test conducted under this protocol.

At least 1 week later, at the beginning of this first experimental visit, demographic data and medical records (confirmed via data entry form), the SGRQ and the Psychological Components Questionnaire will be administered. At this point, participants will receive either a cervical or facial neurostimulator, delivering cervical tVNS or trigeminal TENS. Then, they will undergo a submaximal CWR at 80% of VO_2_ max, with the intervention or the sham, and with the same data measurement of the baseline CWR with the addition of more dyspnoea evaluation questionnaires. These include the Borg scale assessed every minute during the test, the mMRC and CAT questionnaires administered before the test, and the VAS recorded before and after CWR. Participants’ expectations regarding the efficacy of the intervention will be assessed at rest, both with and without stimulation. At the end of the protocol, stimulation and perceived efficacy will be evaluated to gather additional subjective data on relief perception and the quality of the sham. Additionally, the time taken to return to the initial Borg score at rest following CWR will be measured. Vital signs, including SpO_2_, HR, BP, RR and T° will also be monitored throughout the entire duration of the test (except BP and T° that are only assessed before CWR).

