Within 2 weeks after the first experimental visit, those who received an intervention (tVNS or trigeminal TENS) will receive the sham, and those who received the sham will receive an intervention. This switch occurs according to the randomisation process of the cross-over group assignment (figure 1). They all undergo a final submaximal CWR, with data collected in the same sequence during the first experimental visit.

In case of technical issues or other concerns affecting the validity of the test or the data collected during one of the visits, an additional visit (W4) could be added after the last experimental visit. If this visit takes place, it will follow the same exercise testing and intervention protocols as the two preceding experimental visits.

If patients experience significant discomfort or adverse effects during the test or interventions, they should immediately inform the healthcare provider so that appropriate measures can be taken to reassure and manage the patient effectively, including possibly stopping the procedure if necessary. The exercise test termination criteria, established by the *American Thoracic Society*, will be followed to ensure participant safety.^56^ Otherwise, common short-term side effects will be assessed frequently, with a minimum of one evaluation at the end of each experimental visit using a standardised questionnaire designed for the interventions of the study. This approach aims to promptly identify and screen for any undesirable effects experienced by participants (online supplemental appendix 10).

Study visits will be completed before starting or before completing the 12-week rehabilitation programme, with a minimal interval to allow recovery after exercise testing while limiting external influences on exercise tolerance assessments. The schedule for data collection of each variable is detailed in online supplemental
table 3*.*

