### Assignment of interventions

At visit 1, participants will be randomised, using randomisation function of REDCap, to one of four groups for subsequent study procedures: TENSac (visit 2 active → visit 3 sham) or TENSsa (visit 2 sham → visit 3 active), VNSac (visit 2 active → visit 3 sham) or VNSsa (visit 2 sham → visit 3 active), in a 1:1:1:1 ratio through the randomisation function of REDCap. A non-blinded investigator will run the randomisation and allocation process. Given our small sample size (n=8), no stratification will be applied for randomisation.

However, in a future randomised controlled trial, the randomisation should be minimised for FEV_1_ (<35% or ≥35% predicted), sex (one female participant (n=1) and one male participant (n=1), for a total of two participants per group arm (n=2) of the randomisation) and the number of severe exacerbations in the preceding 12 months (0 or ≥1 events).

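### The analysts, as well as the data collectors, know the condition, while the exploratory analysis list and the repeat-visit rule leave choices open; coding the labels and tightening the repeat-visit rule cost little

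*Protocol article*

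**What the plan says.** Under Trial design and study setting, the Protocol article describes a single-blind trial. Of the staff it says that "the researchers in charge of data collection or of the analysis are not blinded". Masking covers the patients only: "participants are unaware if they are receiving the sham or the real interventions". Under Assignment of interventions, "A non-blinded investigator will run the randomisation and allocation process".

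The active-sham contrasts appear under Outcomes (Exploratory) and Statistical analyses. They comprise maximum Borg score, Borg slope from a linear mixed model, pedalling time, paired t-tests of parameters with and without intervention, and an unspecified set of other analyses of the collected data. During the constant work rate test the schedule has the "Borg scale assessed every minute during the test".

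Under Schedule of visits, W4 may be added "In case of technical issues or other concerns affecting the validity of the test or the data collected during one of the visits". If it takes place, "it will follow the same exercise testing and intervention protocols as the two preceding experimental visits".

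The limitations (the strengths-and-limitations box and the Discussion) cover the small sample, learning bias, unblinding of participants through the cross-over, and the unvalidated sham. Neither place mentions unblinded collection or analysis.

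**The concern.** Sham control and participant blinding are there to make the two sessions comparable. Two later steps can undo part of that if the people taking them know which session was active.

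- **Choice of analysis.** The exploratory list is open, so which further comparisons are run and emphasised is decided after the data exist, by someone who can see which direction favours the device.
- **Choice of session.** The W4 trigger reaches beyond technical faults to other concerns about validity. The text does not say that the reason is recorded before the results are seen, whether W4 replaces or supplements the earlier data, or which condition it repeats.

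What is at stake is the exploratory signal. The Introduction says the trial looks for early indications that the methods reduce dyspnoea, and the Discussion says it should guide larger studies. A selected signal would mislead that planning, and a tilt in one direction does not shrink as patients are added.

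**Working it through.** **1. What the plan fixes.** Eight patients over four sequence groups at 1:1:1:1 gives 8/4 = 2 per sequence and 8/2 = 4 per device, as the plan states. No power, alpha, SD or effect size stands behind n=8, so there is no calculated figure to reproduce. The Borg MCID is 1.

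**2. The W4 sentence against the design.** Figure 1 and Assignment of interventions give each patient one active and one sham session, at visits 2 and 3 in either order. The W4 sentence refers to the intervention protocols of those two visits together. They are opposite by design, so the sentence does not determine the W4 condition.

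**3. Leverage of one session.** If substituting W4 changes one patient's active-sham difference by d, the mean of that device group changes by d/4. For an illustrative d = 2 Borg units, 2/4 = 0.5, half the MCID. A shift of the full MCID would need d = 4.

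**4. Effect of a systematic tilt (illustration only).** Assume no true effect, a two-sided 5% paired t-test, an SD of paired Borg differences of 1 to 2, and a tilt of b points. The document gives none of these values. The noncentrality is b√n/SD. The 95% CI half-width is t(0.975, n−1)·SD/√n. The chance that the mean difference reaches the MCID is 1 − Φ((1 − b)√n/SD).

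| n | SD | CI half-width | Rejection, b=0 | b=0.25 | b=0.5 | P(mean ≥ 1), b=0 | b=0.25 | b=0.5 |
|---|---|---|---|---|---|---|---|---|
| 4 | 1.0 | 1.59 | 5% | 6.5% | 11.1% | 2.3% | 6.7% | 15.9% |
| 4 | 1.5 | 2.39 | 5% | 5.7% | 7.7% | 9.1% | 15.9% | 25.2% |
| 4 | 2.0 | 3.18 | 5% | 5.4% | 6.5% | 15.9% | 22.7% | 30.9% |
| 8 | 1.0 | 0.84 | 5% | 9.4% | 23.2% | 0.2% | 1.7% | 7.9% |
| 8 | 1.5 | 1.25 | 5% | 7.0% | 13.0% | 3.0% | 7.9% | 17.3% |
| 8 | 2.0 | 1.67 | 5% | 6.1% | 9.4% | 7.9% | 14.4% | 24.0% |

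The n=8 rows assume that the two devices are pooled. With n=4, imprecision dominates: the half-width is 1.6 to 3.2 points, and a 0.5-point tilt raises the rejection rate only to 6.5–11.1%. The chance of a mean that looks clinically relevant rises more, from 2.3–15.9% to 15.9–30.9%. In a trial this small, that point estimate is what readers are likely to take forward.

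**The case against.** The strongest reply is that single-blinding is openly declared, that the primary outcome is a completion proportion analysed descriptively, and that the Sample size section disclaims any efficacy aim. This stands. It confines the point to exploratory results and sets its priority.

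Four stronger readings are tempting, and the document does not support them.

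- **That every active-sham comparison is biased.** Borg and VAS are rated by participants who are meant to be blinded, and readings such as SpO2 and heart rate are less open to staff expectation. Encouragement during the test is plausible as a route to longer pedalling, but the article does not mention it.
- **That unblinded staff decide on W4.** The text names no decision-maker. The trigger is also limited to concerns about the validity of the test or the data, so repeating a session because its result was unfavourable is a possibility, not something the plan provides for.
- **That masking the person who takes the scores needs no new staff.** TENS is "administered or expertly guided by a physiotherapy expert using the methods of this device", and tVNS is described in similar terms, so the operator may be a member of the research team. The tVNS device is held by hand at the neck. A separate masked rater could need a second person at each session, and patients who feel a strong or a mild stimulus may reveal the mode. The trial is also already recruiting, and a change of rater procedure midway would make early and late patients differ.
- **That a bias of known size has been shown.** The tilts of 0.25 and 0.5 and the 2-unit session are assumed values.

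None of this answers the case for masking the analyst or for a firmer W4 rule. Neither needs extra staff at the sessions.

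**Conclusion.** The point holds for the exploratory contrasts. Analysts and collectors are unblinded without a stated reason or an acknowledged limitation, and the open analysis list and W4 rule give that knowledge somewhere to act. The W4 wording is ambiguous on its face, whoever decides. The completion proportion is not an active-sham contrast and is largely unaffected.

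The size of any bias is not estimable from the document. The one figure that needs no variance assumption is leverage: each unit of change in one patient's difference moves a four-patient mean by 0.25. The table rests on assumed SDs, alpha and tilts, and shows what could happen, not what will. Low to moderate priority.

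**What to change.** 1. **Mask the analysis.** Export the dataset with conditions coded A/B and the sequence-group labels recoded. The non-blinded investigator who runs the randomisation holds the key until the analysis script is locked.
2. **Tighten W4.** Record why a visit is judged invalid before its Borg and pedalling-time results are reviewed, keep the data of that visit, and report the contrasts with and without W4. Reconcile the W4 sentence with the cross-over design so that it states which condition is repeated.
3. **Disclose.** List unblinded outcome collection as a limitation. Separate the device operator from the score collector only where existing staffing already allows it.

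The cost is some protocol wording and slightly more data handling. Analysis follows data collection in the stated timetable (1 February 2026 for collection, 1 May 2026 for analysis), so the coded export fits that schedule. Two limits remain. Masking is incomplete if the analyst also attended sessions. Whoever took the scores will already have heard them, so item 2 guards against later review of the results and not against all knowledge of them.
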